### Outcome measures

Participants will be prompted by email to complete the assessments in an online, secure environment (www.surveygizmo.eu). The order of the assessments will be consistent across all participants and all time-points. If participants do not complete measures within 2 days they will receive further email reminders. The full battery of questionnaires amounts to around 100 items in total, and takes 20–25 minutes to complete. We have evidence from a recently completed protocol that data on such measures can be successfully collected online [40]. Demographic and descriptive clinical data will be gathered at baseline only. Measurements to permit health economic evaluation will form part of the descriptive demographic data, with some aspects audited at each assessment point (e.g. medication use, visits to health professionals, other health care utilisation). Descriptive data on health behaviours such as smoking and alcohol use will also be reported.

The co-primary measures that relate to functional health and well-being will be the Patient Reported Outcome Measurement Information System: Global Health scale [41] (PROMIS-10), the Warwick-Edinburgh Mental Well-being Scale [42] (WEMWBS) and the Glasgow Sleep Impact Index [43] (GSII). The PROMIS-10 is a reliable (*α* ≥ .92) but brief (10 items), generic measure that has proven to be very useful in measuring outcomes in clinical trials (http://www.nihpromis.org/science/). It can also be used to estimate cost-utility using QALYs (quality-adjusted life-years) [44, 45]. The WEMWBS is a short (14 items) and psychometrically robust measure (*α* ≥. 91) of mental well-being and is included because it focuses entirely on positive aspects of functional mental health. A previous pilot trial suggests the WEMWBS is sensitive to changes after CBT for insomnia [46]. The GSII is a patient-reported outcome (PRO) measure that asks patients to individually generate, and then assess, three domains of sleep-related impairment unique to their own individual context. Its strength is ecological validity and the GSII has been shown to be sensitive to change following CBT [43]. This combination of PRO, generic functional health status, and positive mental state (rather than symptom reduction) matches our intention to evaluate the impact of dCBT upon quality of life domains.

Secondary outcomes relate to specific measurement of the six areas of daytime consequence that are associated with the clinical diagnosis of insomnia disorder [1, 14, 47]. These are mood (Patient Health Questionnaire (PHQ-9: 9 items [48]) and Generalised Anxiety Disorder (GAD-7: 7 items [49])); energy (Flinders Fatigue Scale (FFS: 7 items [50]); relationship satisfaction (Relationship Assessment Scale (RAS: 7 items [51]); cognitive functioning (Cognitive Failures Questionnaire (CFS: 25 items [52])]; work performance and satisfaction (Work Productivity and Activity Impairment questionnaire: Specific Health Problem (WPAI:SHP: 6 items [53]), 1 item on job satisfaction [54]); and sleepiness (Epworth Sleepiness Scale (ESS: 8 items [55]). As an exploratory measure, participants will also complete 1 item about their general life satisfaction [56].

In order to appraise the mediating effects of sleep improvement per se we will use the SCI [35] and estimates of sleep diary parameters [57]. The SCI is an internally consistent (*α* = .86) measure with a clinical cut off that can correctly identify 89 % of those with probable DSM-5 insomnia disorder. The SCI and sleep diary variables have proven to be sensitive to change following dCBT [34].

In addition to these formal assessments the web/mobile platform will provide online analytics for the dCBT group. These can be used, for example, to measure the process of change (sleep diary) and to monitor how many sessions were completed and the number of weeks to complete the course. These will be used in exploratory analyses. We will also gather information on the demographics of the sample, employment, work satisfaction and economic outcomes, their health characteristics, and their use of clinical services during the period of their trial participation.

### Assessment of safety

The likelihood of serious adverse events occurring during this trial is low since dCBT for insomnia has not been reported to cause them. The intervention offered in the trial has previously been tested in a RCT testing change in insomnia and no adverse outcomes were reported [29, 34]. However, studies have shown that daytime sleepiness and vigilance impairment may increase during sleep restriction therapy (SRT) (one component of CBT-I), owing to restricted sleep opportunity [58]. We will record the occurrence of any serious adverse events in trial participants, defined as: (1) all deaths, (2) suicide attempts, (3) serious violent incidents, (4) admissions to secure units, and (5) formal complaints about the online intervention. Owing to the online nature of the assessments and intervention, it is unlikely that the research team will become aware of all such events. At the end of treatment we will also ask participants to complete an adapted version of a previously employed adverse effects measure [59] to assess differential rates of self-reported adverse effects.

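### The serious-event list leaves out the likely consequences of the risk the protocol names, counts formal complaints, and adverse effects are asked about only once, at end of treatment

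*Protocol article*

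**What the plan says.** All of the following is in the Protocol article.

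- **Named risk.** Assessment of safety cites evidence that "daytime sleepiness and vigilance impairment may increase during sleep restriction therapy". Sleep restriction is part of the tested programme (Planned intervention).
- **Definition of serious adverse events.** The same section defines them by a closed list: "1) all deaths, (2) suicide attempts, (3) serious violent incidents, (4) admissions to secure units, and (5) formal complaints about the online intervention".
- **Capture of those events.** Because the trial runs online, the section accepts that "it is unlikely that the research team will become aware of all such events". It describes no question put to participants about these events.
- **Adverse effects.** "At the end of treatment we will also ask participants to complete an adapted version of a previously employed adverse effects measure"; the purpose is "to assess differential rates of self-reported adverse effects". The current study places end of treatment at 8 weeks.
- **Schedule.** Assessment points gives weeks 0, 4, 8 and 24, with week 4 labelled mid-treatment. Planned intervention allows dCBT access for up to 12 weeks.
- **Related measurements.** Outcome measures lists the Epworth Sleepiness Scale and the Cognitive Failures Questionnaire as secondary outcomes. Data for the health economic evaluation, such as medication and health-care use, are collected "with some aspects audited at each assessment point".

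**The concern.** The safety definition does not follow from the risk stated just before it. If sleepiness and impaired vigilance are the expected harm, the events that would make that harm serious are accidents at the wheel, at work or at home, injuries, and the admissions that follow. None of these is on the list unless fatal. Better reporting would not repair this, because a non-fatal accident does not qualify however well it is reported.

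A formal complaint, by contrast, does qualify although it is not a health event. If the phrase about the online intervention means dCBT, complaints can arise mainly in one arm, and a between-arm count of serious events would then mix dissatisfaction with harm.

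Timing is the second issue. The risk arises while sleep restriction is under way, but adverse effects are asked about once, at week 8. People who leave before then do not contribute, and anyone still using the programme in weeks 8 to 12 is not asked again. At stake is whether the trial can describe the consequences of its one named risk in a population that may be taking medication for sleep or other conditions and is not medically examined (Participants).

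**Working it through.** The protocol states no safety event rate and this point disputes none of its figures. The check is mainly a comparison of passages.

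**Step 1: risk against definition**

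| Plausible consequence of sleepiness or poor vigilance | On the serious-event list? | Collected elsewhere in the article? |
|---|---|---|
| Death | Yes | – |
| Non-fatal accident or injury | No | Not described |
| General hospital admission | No (secure units only) | Possibly within health-care use, as economic data |
| Sleepiness as a symptom | No | Epworth scale, secondary outcome |
| Everyday cognitive lapses | No | Cognitive Failures Questionnaire, secondary outcome |

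The list also holds one item, complaints, that is not a health event.

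**Step 2: timing**

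- The risk falls during sleep restriction, within treatment.
- The adverse-effects measure is given at week 8 only; the week-4 assessment is not named for it.
- The sample size section allows for 13 % dropout. Applied to 500 per arm, 500 × 0.13 = 65 people, leaving 435, which agrees with the stated minimum of 433 analysed. On the plan's own assumption, up to about 65 per arm might not supply the single adverse-effects report.
- The current study says that more than 80 % complete the course within 8 weeks. So fewer than 20 % do not, which is fewer than 500 × 0.20 = 100 in the dCBT arm. How many of these would still be in treatment, rather than have stopped, is not given.

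**Step 3: what incomplete capture could cost (illustration only)**

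The documents give neither an accident rate nor a capture rate, so both are assumed here. With n = 500 in the dCBT arm, true rate r and capture fraction c:

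- expected number seen = n × r × c
- chance of seeing at least one = 1 − (1 − r × c)^n

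| Assumed r | c = 100 % | c = 50 % | c = 25 % |
|---|---|---|---|
| 0.5 %: expected number | 2.5 | 1.25 | 0.625 |
| 0.5 %: chance of at least one | 92 % | 71 % | 46 % |
| 1 %: expected number | 5 | 2.5 | 1.25 |
| 1 %: chance of at least one | 99 % | 92 % | 71 % |

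This shows only how the result depends on capture. For an event that is not on the list, the number entering the serious-event count is zero at any capture fraction.

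**The case against.** The strongest reply is that the named risk is in fact measured. The Epworth scale and the Cognitive Failures Questionnaire go to both arms. There is a mid-treatment assessment, and Outcome measures says the instruments keep the same order at every time-point. The natural reading is that both are collected at week 4, although the article has no table of instruments by visit. This stands: a reader might infer that the trial misses the sleepiness hazard altogether, and the document does not support that. It does not settle the matter, because neither scale is described as recording accidents or injuries as safety events. The protocol also frames sleepiness as an expected benefit at week 8. A better mean at week 8 can coexist with a temporary mid-treatment worsening, or with injury in a few people.

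Second, admissions are not wholly absent. Secure-unit admissions are listed, and health-care use is asked about at each assessment. This also stands, but those data are described as economic, and nothing brings a general admission into safety reporting.

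Third, the adverse-effects measure adapts a published instrument whose items and recall period are not shown. It may ask about the whole treatment period, and it may ask about sleepiness. This stands as well: one cannot say that it is unable to pick up mid-treatment effects. What can be said is that it relies on one report at week 8, from those still responding.

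Fourth, the article openly admits incomplete awareness, excludes people who report excessive sleepiness at entry, and may condense a fuller safety procedure. For that reason the point rests on the stated list and the stated timing, not on procedural detail that a fuller document might hold.

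**Conclusion.** The point holds in a limited form. The closed list omits accidents, injuries and general hospital admissions, which are the plausible consequences of the protocol's own named risk, and it includes complaints. No active question about serious events is described, their capture is acknowledged to be incomplete, and adverse effects are asked about once although a week-4 assessment exists and access extends to week 12. The defect lies in safety consequences and their timing.

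Its size cannot be stated from the document; the capture table rests on assumed rates.

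Two stronger conclusions are tempting and are not supported:

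- **That capture differs by arm.** dCBT has daily prompts and a moderated community, while SHE is a website. But the programme is fully automated, the research team has limited contact with participants, and the article does not say that the platform or its moderators report events to the trial. Unequal capture is possible, not shown.
- **That the trial will probably report no safety signal.** Without an event rate or a capture rate this is a guess. An upper bound from a zero count in 433 people would not help either: 433 is the efficacy target, and the bound says nothing about how large this gap is.

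This is a worthwhile, inexpensive improvement and does not threaten the primary efficacy analysis. It assumes that the list is meant as complete, as its wording suggests, and that end of treatment means week 8.

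**What to change.** In both arms, with identical wording:

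1. Add a few items on accidents or injuries attributed to sleepiness, and on hospital admissions, to the existing week-4, week-8 and week-24 online assessments, beside the health-care-use questions. Count the answers in safety reporting.
2. Give the adverse-effects measure at week 4 as well as week 8.
3. Report week-4 Epworth scores by arm as a safety outcome. If the scale is already collected then, as seems likely, this changes reporting only.
4. Report formal complaints separately from serious adverse events, and state whether the item covers dCBT only or the SHE website too.

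The cost is a slightly longer battery, now about 100 items and 20 to 25 minutes, and an ethics notification. Treatment, randomisation and the primary analysis are unchanged.

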### Sample size calculation

Our planned primary intention-to-treat analyses will compare dCBT + TAU versus SHE + TAU for each of the three primary outcomes separately. Assuming a significance level of 1.667 % (adjusted from 5 % because of having three primary outcomes) and a power of 90 %, to detect a standardised effect size of 0.25 we require a minimum of 433 participants in each of the groups in the analysis. Accounting for a conservative dropout rate of 13 %, we will recruit 500 participants in each treatment group, or 1000 participants in all. This sample size will have more than 80 % power to detect a large-sized indirect effect through the sleep mediator (proportion mediated approximately 75 %) for each between-group comparison. We believe that a sample of this size is feasible to recruit for two reasons. First, online/mobile interventions are much more accessible than in person interventions; and second, published research using dCBT has already shown that large samples may be recruited over comparatively short recruitment periods.

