### The current study

This study seeks to ascertain the impact of improved sleep on three key areas of quality of life: functional health status, patient-generated (sleep-related) quality of life impairment and psychological well-being. Over the past 5 years, self-help CBT delivered via the Internet has been introduced, not least because of the importance of widening access to effective psychological therapy. Several randomised controlled trials (RCTs) have evaluated digital CBT (dCBT) applications; each of which has found moderate to large improvements in insomnia symptoms relative to waitlist groups [32–34]. Only one programme, however, has been tested versus a placebo intervention, demonstrating significant and sustained improvements in sleep continuity; for example, sleep diary-assessed sleep efficiency, sleep onset latency and wake time after sleep onset, and self-reported global sleep quality [34]. It is this dCBT intervention that will be used in the present study. Data from the programme show that more than 80 % of participants complete the course within 8 weeks.

The primary hypotheses for the trial are that, compared to sleep hygiene education (SHE):The dCBT intervention will be associated with improved functional health status by the end of treatment (8 weeks)The dCBT intervention will improve positive psychological well-being by the end of treatment (8 weeks)The dCBT intervention will be associated with reduced patient-generated sleep-related quality of life impairment (8 weeks)The effect of dCBT on outcomes (8 weeks) will be mediated by sleep status during the treatment phase (4 weeks)

The secondary hypotheses are that, compared to SHE:The dCBT intervention will be associated with reduced symptoms of negative mood, fatigue and relationship/social dysfunction by the end of treatment (8 weeks)The dCBT intervention will be associated with reduced problems with sleepiness, cognitive impairment and productivity by the end of treatment (8 weeks)Improvements will be maintained at follow-up (24, 36, 48 weeks)The effect of dCBT on longer-term outcomes (24, 36, 48 weeks) will be mediated by sleep status during and upon completion of the treatment phase (4, 8 weeks)

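### Holm's step-down could replace the fixed Bonferroni level for the three primary outcomes: the same 5 % familywise error, never fewer rejections, and an optional gain in power

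*Protocol article*

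**What the plan says.** The section Sample size calculation of the Protocol article says that the primary intention-to-treat analyses will compare the arms "for each of the three primary outcomes separately". It uses a level of 1.667 %, lowered from 5 % "because of having three primary outcomes", and 90 % power "to detect a standardised effect size of 0.25". From this it concludes: "we require a minimum of 433 participants in each of the groups in the analysis". After an allowance of 13 % for dropout, it sets recruitment at 500 per arm.

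The three outcomes are PROMIS-10, WEMWBS and GSII. The section Outcome measures labels them co-primary, and The current study gives each its own primary hypothesis.

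The section Statistical analysis specifies ANCOVA at 8 weeks with the baseline value of the outcome as covariate. It names no multiplicity procedure. No section requires all three outcomes to be significant.

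**The concern.** Dividing 5 % by three and holding every outcome to 1.667 % is the plain Bonferroni rule. It takes no account of what has already been rejected. Once one null hypothesis is rejected, at most two can still be true, so a level of 1.667 % for the rest is stricter than 5 % familywise control needs. Holm's procedure uses that slack.

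At stake is the chance of supporting a second and a third claim in a trial whose stated aim is broad: "This study seeks to ascertain the impact of improved sleep on three key areas of quality of life". An outcome with p between 1.667 % and 5 % can fail under Bonferroni and pass under Holm, with no more participants and no higher familywise error.

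**Working it through.** **1. Reproduce the plan's figure.** Inputs from Sample size calculation: level 0.05/3, power 0.90, effect 0.25 SD. Two-sided testing is inferred, because a one-sided level would give 373 per arm.

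n per arm = 2 × (z₁₋α/₂ + z₁₋β)² / d² = 2 × (2.394 + 1.282)² / 0.25² = 432.3, so 433. This matches. (The noncentral t distribution gives 434, which is no material difference.)

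Dropout: 433 / 0.87 = 497.7, so 498, rounded up to 500. This also matches. Power per outcome at 433 is 90.05 %.

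**2. Error rate of Holm.** Suppose m of the three null hypotheses are true. When Holm first rejects a true null, at least m hypotheses are still untested or being tested, so the threshold in force is at most 0.05/m. A false rejection therefore needs at least one of the m true-null p-values to be at or below 0.05/m. The probability of that is at most m × 0.05/m = 0.05, whatever the correlation. Simulation agrees: 4.9 % (correlation 0) and 4.5 % (0.5) with no true effects, and 4.3 to 4.8 % with effects on one or two outcomes.

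**3. Why Holm never loses a rejection.** Its thresholds are 1.667 %, 2.5 % and 5 %, and none is below 1.667 %. Any outcome with p ≤ 1.667 % is therefore rejected. The chance of rejecting at least one is identical under both rules, because both need the smallest p-value to be ≤ 1.667 %.

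**4. Power with equal effects.** Test statistics were simulated as trivariate normal with mean 0.25 × √(433/2) = 3.678 and a common correlation ρ. The document does not give ρ, so a range is assumed.

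| ρ | Per outcome, Bonferroni | Per outcome, Holm | All three, Bonferroni | All three, Holm |
|---|---|---|---|---|
| 0 | 90 % | 95.2 % | 73.1 % | 87.4 % |
| 0.3 | 90 % | 94.7 % | 75.9 % | 88.2 % |
| 0.5 | 90 % | 94.3 % | 78.3 % | 89.1 % |
| 0.7 | 90 % | 93.8 % | 81.2 % | 90.2 % |
| 0.9 | 90 % | 92.9 % | 85.1 % | 91.7 % |

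**5. Unequal effects, ρ = 0.5.** If only one outcome has a true effect of 0.25 SD, its power goes from 90.0 % to 90.2 %. If two have it, the power of each goes from 90.1 % to 92.0 %.

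**6. Baseline adjustment.** The planned test is ANCOVA. If 0.25 is in raw SD and baseline correlates r with the 8-week value, the mean of the test statistic becomes 3.678 / √(1 − r²). The document gives neither r nor the scale of the 0.25. For r = 0.5 the mean is 3.678 / √0.75 = 4.248. With ρ from 0 to 0.7:
- Power per outcome is 96.8 % under Bonferroni and 98.4-98.8 % under Holm.
- Power for all three is 91-93 % under Bonferroni and 97 % under Holm, a gain of about 4-6 points.

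For r = 0.6, power for all three is 96-97 % against 99 %.

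**The case against.** The strongest reply is that nothing here is wrong. Bonferroni is valid, the trial was sized at the adjusted level, and the arithmetic is correct. This stands in full.

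A second reply is that 1.667 % appears as a sizing assumption, while Statistical analysis names no procedure. Sizing at 5 %/3 is compatible with a Holm analysis, and an analysis plan that is not shown may already specify one. This stands in part. Bonferroni is the natural reading, because the same paragraph describes the planned primary comparisons, but the article does not state a fixed testing rule outright.

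A third reply is that the gain depends on the case assumed. This also stands: it is largest when all three outcomes respond, the correlation is low and baseline adjustment adds little.

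A reader might go further and infer that the trial is underpowered for its aim, because the chance of confirming all three outcomes is well below 90 %. The document does not support that. The outcomes are compared separately, each has its own hypothesis, and no section makes joint success a criterion. The 90 % can be read as per outcome from the sentence before it. The 73-81 % also applies only if baseline adjustment gains little or 0.25 is already in residual SD. With r = 0.5 on a raw-SD effect, Bonferroni already exceeds 90 % for all three.

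**Conclusion.** The point holds as an optional improvement. At the same two-sided 5 % familywise error, Holm rejects whatever Bonferroni rejects and sometimes more.

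The size depends on three things that the document does not give: the correlation between outcomes, how many outcomes truly respond, and whether 0.25 is a raw or a residual SD. In the most favourable setting (0.25 SD on all three, no gain from adjustment, correlation 0 to 0.7) the gain is about 4-5 points per outcome and 9-14 points for all three. In less favourable settings it shrinks to a few points or to almost nothing. It is never negative, and power for at least one outcome does not change.

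The sample size is right and the planned level is valid. Neither the choice of Bonferroni nor the joint power is an error in the plan.

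**What to change.** Add one sentence to Statistical analysis, before anyone deciding on it has seen outcomes: the three primary outcomes are tested with Holm's step-down procedure at two-sided familywise 5 %, and a significant result supports a claim for that outcome only. Keep 1.667 % in Sample size calculation as a conservative sizing level, with 433 analysed and 500 recruited per arm unchanged. If an analysis plan already names a step-down test, align the article's wording with it.

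The cost is in interval estimation. Bonferroni comes with simple simultaneous 98.33 % confidence intervals, and intervals that match Holm are less simple. Report 98.33 % intervals beside the 95 % ones, and note that neither set need agree with the Holm decision for every outcome. If the team values matching intervals more than the extra power, keeping Bonferroni is a legitimate choice.
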